### 2.6. Intervention

The 12-week intervention (Sit Less program) will consist of four components based on the Habit Formation framework (Fig 3). Previous studies have shown significant (91 minutes/day) reductions in sedentary time following 4 to 24 weeks of intervention [29].

**Fig 3 pone.0302582.g003:**
[figure not shown]
Overview of multiple-technology-based sedentary behavior reduction intervention.

The Habit Formation framework suggests that 12 weeks is required to develop a new habit [30]. We therefore propose a 12-week intervention period.

#### 2.6.1. Theoretical framework

The Sit Less program employs a Habit Formation framework [31] to target the habit-like nature of sedentary behavior, which often occurs without conscious thought or intention [32, 33]. The program focuses on making individuals aware of their sedentary habits and encourages the adoption of new behaviors, such as taking breaks to stand or walk, through consistent practice in specific contexts. According to the Habit Formation framework [31], habit formation involves four phases: motivation, action initiation, behavior repetition in a context, and cue-association building. Through this process, over time individuals may rely on contextual cues rather than conscious self-regulation to initiate a behavior, making it potentially easier to perform and more sustainable with consistent environments [31]. The Habit Formation framework is widely used for sedentary behavior reduction in older adults [32].

The framework guides our intervention by: 1) bringing sedentary behavior into conscious awareness through prompts (e.g., vibrations from a Fitbit), and 2) making a new habit of sedentary breaks (5 minutes of standing/walking every 30 minutes of sitting) through context-dependent repetition (e.g., during TV commercials). To enhance habit formation, behavioral techniques supporting motivation and action planning will be used (Table 1) [34].

**Table 1 pone.0302582.t001:** Relationship between intervention components, theoretical constructs, and behavioral techniques.

Intervention component	Theoretical constructs	Behavioral change techniques
**Instructional/ goal setting session**	Motivation, define context and target habitual behavior	Goal setting, instruction on how to perform behavior, information on health consequences, identification of targetable prolonged sitting
**Activity tracker**	Awareness of unconscious sitting habits, gradually develop a new habit of sedentary breaks through repetition, develop a contextual cue-behavior association	Use of sedentary break prompts and cues, context-dependent repetition, self-monitoring, feedback on behavior
**Smart water bottle**	Motivation (I have to get up to go to the restroom), gradually develop a new habit of drinking water	Use of cues through change of bottle color (time to drink water)
**Weekly tailored text message**	Motivation, translate intention into action, enhance contextual cue-behavior association	Feedback on behavior, problem solving, review of goal, setting of new goal

#### 2.6.2. Instructional goal setting session

The PI will provide an instructional goal setting session during Baseline Visit 2. The PI will review the prior 7 days of activPAL3 data and identify targetable prolonged sedentary bouts with the participant. The PI and the participant will set two goals: 1) a sedentary behavior reduction goal aimed at reducing daily sedentary time gradually until they reach the goal of ≥ 120 minutes of sedentary time reduction; and 2) a sedentary break goal of 5 minutes of standing/walking every 1 hour and then increasing its duration to 10 minutes and frequency of the sedentary break to every 30 minutes [35]. These goals have been demonstrated to be feasible in stroke patients and CVD patients [8, 21]. Participants will have the autonomy to set their weekly goals, whether to maintain the same target as the previous week, or reduce sedentary time. We do not recommend reducing sedentary time by more than 30 minutes per week, but adjustments can be made based on the participants’ current sedentary hours and willingness.

In addition, the participant will be given the Ten Top Tips (TTT). The TTT is a booklet developed from the Habit Formation Theory and includes tips to add sedentary breaks into their daily routine [36]. The original TTT booklet [36] was obtained from [name] [36], one of the developers of the Habit Formation theory [31], and it was applied to sedentary behavior with permission to revise it for the current study. The original TTT booklet suggested limiting TV watching to no more than one hour at a time and promoting light physical activities such as walking—by leaving the remote control by the TV, standing up during commercials, opting for stairs, and parking at a distance from the entrances of malls or offices [36]. It also included recommendations for stretching and muscle strengthening exercises [36]. We revised the original TTT booklet to include 8 tips, excluding the stretching and muscle training recommendations and incorporating the Fitbit and smart water bottle into daily routines. Although the suggested tips involve only light levels of physical activity, such as standing and walking for 3 to 5 minutes every hour—activities with no more risk than those encountered daily—we will instruct participants to stop these exercises immediately if they feel unwell or experience discomfort, and to promptly seek medical advice.

#### 2.6.3. Activity tracker

A Fitbit Inspire 2 (Fitbit Inc., U.S.A) will be provided to each intervention participant. This device alerts participants with a vibration and message on the watch face when they have been sitting for 60 minutes (i.e., “Move alert”). Participants can select the days and the time ranges to receive the move alerts. Fitbit provides sedentary behavior statistics including the longest sitting period (“Longest Stationary Period”) and total daily sitting hours (“Stationary Hours”) in the app. Participants will be encouraged to check the Fitbit app at the end of the day to monitor their longest sitting period and total daily sitting hours. They will be guided to apply the TTT booklet tips to interrupt their longest sitting period and decrease total daily sitting hours, aiming to achieve their overall goals of a total of 120 minutes of sedentary behavior reduction and having 5 minutes of a sedentary break every 30 minutes by the end of the intervention.

To ensure consistent use of the Fitbit, participants will be instructed to wear the device during waking hours, including while showering or swimming. They will also be encouraged to wear the Fitbit at night, although this is optional. Participants are required to charge the Fitbit once a week, and we will send a text message every Sunday reminding them to charge and sync their Fitbit. We will track participants’ wear status over 12 weeks. If a participant fails to sync their Fitbit or wear it for two consecutive days, they will receive an automated reminder text message. If no improvement is observed within another two days, research staff will contact the participant by phone to troubleshoot issues.

#### 2.6.4. Smart water bottle

We will provide a smart water bottle (HidrateSpark, U.S.A) to each participant in the intervention group as a natural motivator to have sedentary breaks. The device alerts participants with a color change and message on the Fitbit to keep them hydrated. The device provides the daily water intake summary in the Fitbit app. The app calculates an individualized water intake goal based on the participant’s weight, age, and activity levels. By increasing water intake, participants will need to get up more frequently to use the bathroom and to refill their water bottles, which will break their prolonged sedentary behavior.

#### 2.6.5. Tailored text messages

Three text messages each week will be provided to support and enhance the habit formation process. Using data collected from the Fitbit device, participants will receive algorithm-derived, individually tailored text messages updating them on their weekly goal progress mid-week and a review of sedentary behavior at the end of the week. We will start each week on Monday and provide an end of week message on Monday morning. A midweek message will be sent on Thursday. Thursday’s message will provide midweek sedentary behavior feedback. Sunday’s message will encourage participants to achieve their goal and sync the Fitbit to the app. Monday morning’s (end-of-week) message will be structured by 1) algorithm-derived feedback (praise, reinforcement or encouragement messages), 2) a weekly summary of sedentary time, the longest sedentary period, and a suggestion for extra sitting breaks, 3) one tip from the TTT booklet, and 4) setting of next week’s goal on sitting hours, duration, and frequency of sitting breaks (Table 2).

**Table 2 pone.0302582.t002:** Examples of praise, reinforcement, and encouragement messages. The underline indicates personalized information.

Praise message If the participant achieves this week’s sedentary hours goal for > 5 days	Reinforcement message If the participant achieves this week’s sedentary hours goal for 3–5 days	Encouragement message If the participant achieves this week’s sedentary hours goal for < 3 days
Cheers to you on a job well done, Jane! You completed your daily sitting goal for 6 days. You spent 8.7 hours sitting daily. You could take extra breaks from sitting 19:00–19:45 on weekdays. Take a stand today! Challenge yourself to stand while talking on the phone.	You’re on the right track, Jane! You completed your daily sitting goal for 4 days during Week 1. You spent 9.8 hours sitting daily. You could take extra breaks from sitting 19:00–20:10 on weekdays. If you’re watching TV today, remember to get up and take a short walk during commercial breaks!	A little bit of effort goes a long way, Jane! You completed your daily sitting goal for 2 days. You spent 11 hours sitting daily. You could take extra breaks from sitting 19:00–20:40 on weekdays. A great way to break your sitting is to do some chores around the house. Meet your goals and get things done!

To develop and provide text messages, we will take the following steps.

**1. Creation of weekly text message template:** The team will create the weekly message templates for praise, encouragement, and reinforcement messages.**2. Fitbit data transfer:** We will transfer the Fitbit data from the participants’ Fitbit accounts into REDCap on Thursday morning and Monday morning to provide Thursday (mid-week) and Monday (end-of-week) messages. There are several Fitbit data management platforms that summarize physical activity data, but none summarize sedentary behavior data. Therefore, the team developed our own data collection interface using Fitbit’s Web Application Programming Interface (API). This platform provides secure data acquisition and management tools that facilitate remote data collection from Fitbit. All Fitbit’s minute-level data will be imported into REDCap.**3. Fitbit data aggregation and calculation:** Fitbit provides minute-level data of prelabeled “sedentary” time and step counts, as well as summary data for “light level”, “moderate”, and “vigorous” activity time, and does not provide meta-data shown in the Fitbit app (“longest stationary period” and “total stationary hours”), nor an algorithm to replicate the daily sedentary behavior meta-data. Therefore, we will reproduce the Fitbit app’s sedentary behavior meta-data. First, we will exclude days with less than 10 wearing hours [37] and remove the sleep period detected by Fitbit from calculation. The “total stationary hours” from Fitbit will be calculated by the sum of all sedentary minutes that had accompanying heart rate data during a selected day. The “longest stationary period” from Fitbit will be calculated by the longest uninterrupted period of the day at which zero steps were taken.**4. Integration of Fitbit data into the text message template**: The team will take advantage of logics built into the REDCap environment to integrate information from the collected Fitbit data into our weekly text message template using the following algorithm. If the participant achieves the week’s sedentary hours goal for > 5 days, they will receive a praise message. If the participant achieves the week’s sedentary hours goal for 3–5 days, they will receive a reinforcement message. If the participant achieves the week’s sedentary hours goal for < 3 days, they will receive an encouragement message. The examples of praise, reinforcement, and encourage messages are provided in Table 2. The text messaging algorithm system has been used successfully before [38].**5. Send text message by using Twilio and REDCap**: The customized text message will be sent to the respective participant using the Twilio plug-in for REDCap.**6. Ask next week’s goals via text message**: This study will use REDCap’s function to administer a survey via SMS conversation to set a participant’s next week’s sedentary hours goal and numbers/frequency of sedentary breaks. Participants may respond to the SMS survey with any kind of alpha-numeric text. Participants’ answers on next week’s goals will be automatically saved into REDCap.

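### The re-created Fitbit longest stationary period has no minute-level wear condition, so an unworn night can be texted to participants as their longest sitting period

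*Protocol article*

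**What the plan says.** Section 2.6.5, step 3, sets out how the app's two sedentary measures will be re-created from minute-level Fitbit data. Two filters come before both measures: "First, we will exclude days with less than 10 wearing hours [37] and remove the sleep period detected by Fitbit from calculation".

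For the longest stationary period, the figure "from Fitbit will be calculated by the longest uninterrupted period of the day at which zero steps were taken". For total stationary hours, by contrast, the count is "the sum of all sedentary minutes that had accompanying heart rate data during a selected day". Only the second of these carries a heart rate condition.

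On wear, section 2.6.3 asks for use during waking hours. Of nights it says: "They will also be encouraged to wear the Fitbit at night, although this is optional". It adds: "Participants are required to charge the Fitbit once a week". Neither the length nor the time of charging is given.

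The longest period reaches participants through the Monday message, which includes "a weekly summary of sedentary time, the longest sedentary period, and a suggestion for extra sitting breaks".

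**The concern.** The two definitions stand next to each other, and only one is protected against non-wear. Requiring heart rate data for total stationary hours makes sense only if some minutes labelled sedentary can occur without the device on the wrist. The same risk applies to a run of zero steps, yet the safeguard is not carried over.

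A participant who follows the instructions fully may take the device off each night. Read literally, the rule can then return the night as that person's longest sitting period. Such a figure would not respond to anything the participant does during the day.

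The longest period is one of the listed items of the weekly feedback. Acceptability is a primary outcome (section 2.9.1). It includes a questionnaire on the text messages that covers the relevance of their content, with a threshold of 75% agreement on each statement. Implausible feedback could lower that result for a technical reason unrelated to the idea being tested.

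**Working it through.** The article states no figure for this measure, so there is nothing to reproduce. The check applies the written rule to example days.

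**Inputs from the article**
- Minimum wear for a kept day: 10 hours (section 2.6.5, step 3).
- Fitbit-detected sleep is removed (same step).
- Longest period: longest zero-step run of the day (same step).
- Night wear optional, charging weekly (section 2.6.3).

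**Assumptions not in the article**
- The day runs from midnight to midnight.
- Off-wrist minutes carry zero steps.
- The true longest seated bout is 100 minutes.
- When the device is worn at night, the whole night is detected as sleep and removed.

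**Step 1: what the day filter leaves in.** Largest unworn time on a kept day = 24 − 10 = 14 hours.

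**Step 2: what sleep removal leaves in.** It removes a night on which the device was worn. With the device off, there is no worn sleep to detect, so the night stays in.

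**Step 3: the rule on example days, as written and with a heart rate condition added.**

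| Day | Worn hours | As written (min) | With heart rate condition (min) |
|---|---|---|---|
| Worn 07:00–22:00 | 15 | 420 | 100 |
| Worn 07:00–22:00, charged 12:00–14:00 | 13 | 420 | 100 |
| Worn 08:00–18:00 | 10 | 480 | 100 |
| Worn day and night, charged 12:00–14:00 | 22 | 120 | 100 |
| Worn day and night, charged 12:00–13:00 | 23 | 100 | 100 |

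The 420 is 00:00–07:00 (7 × 60). The 480 is 00:00–08:00 (8 × 60). The 120 is the two-hour charge (2 × 60), which exceeds the assumed bout of 100. The one-hour charge (60) does not exceed it, so the last row is unaffected. A charging gap therefore matters only when it outlasts the true longest bout.

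**Step 4: how far the error reaches.**
- The sedentary outcomes come from the activPAL (section 2.9.2), not the Fitbit.
- The message tier depends on the sedentary hours goal: "If the participant achieves the week’s sedentary hours goal for > 5 days, they will receive a praise message". The measure behind that goal does carry the heart rate condition.
- The compliance criteria in section 2.9.1 use valid wear days and replies to goal-setting texts.

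None of these uses the longest period.

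**The case against.** The strongest reply is that this is a one-sentence summary of a script. The article does not say whether off-wrist minutes are stored as zero or as missing, and a script could treat missing minutes as breaking a run. The documents cannot settle this, so the result is conditional. But the article does give an explicit rule, and next to it a rule for the sister measure that does include the safeguard. That contrast is in the text and is more than a detail left to a fuller document.

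Several stronger readings are tempting, and the article does not support them.
- A reader might infer that there is no wear filter at all. There is one at day level, and detected sleep is removed. Only the minute-level condition is absent.
- A reader might divide 420 minutes by the 45, 70 and 100 minute windows in Table 2 and call the figure 4.2 to 9.3 times too long. Those windows are examples of when to take extra breaks. They are not labelled as longest periods, so the ratio is not an estimate of error.
- A reader might infer that suggested breaks will fall in sleeping hours. The article gives no rule deriving the break window from this measure.
- A reader might infer that the texted figure will disagree with the app. The article says Fitbit supplies no algorithm, and nothing shows how the app treats off-wrist time.
- A reader might infer that section 2.6.3's advice to interrupt the longest sitting period rests on this figure. There, participants take it from the app.

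The objection also stands on reach: no trial estimate or feasibility criterion is calculated from this measure.

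**Conclusion.** The point holds in a limited form. The written definition of the longest stationary period lacks the minute-level wear condition applied to total stationary hours, and neither prior filter removes a night with the device off. If off-wrist minutes carry zero steps, the Monday message can report an unworn night of about 420 to 480 minutes (assumed wear hours) where the true longest bout might be 100 (also assumed). The number of participants affected is unknown, because the share who remove the device at night is not given and night wear is encouraged.

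The consequence is faulty feedback content, with a possible effect on the acceptability ratings of the text messages. A reader might take this as a threat to the efficacy results. It does not alter the measurement or analysis of the activPAL outcomes, the choice of praise, reinforcement or encouragement message, or the compliance criteria. It is worth correcting because the correction is cheap and the needed condition is already in use.

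**What to change.** In section 2.6.5, step 3, define the longest stationary period as the longest run of zero-step minutes during worn time, with wear shown by the heart rate condition already used for total stationary hours. Set in advance a short tolerance for brief loss of heart rate signal. Without it, one lost minute in the middle of a 100-minute bout would cut the reported period to about 50 minutes ((100 − 1) / 2 = 49.5).

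State how off-wrist minutes appear in the step data. Check the new figure on a few test accounts with the device off overnight, and on a day with a long charge.

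Recruitment began in September 2022, so record the date on which the change takes effect. The cost is minor scripting and a short check. The downside is that earlier and later participants may receive slightly different feedback, and the recorded date lets that be described when acceptability is reported.

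### The Fitbit longest stationary period lacks the minute-level heart-rate check used for total stationary hours, so an unworn night can be reported to participants as sitting

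*Protocol article*

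**What the plan says.** Section 2.6.5, step 3, sets out how the team will reproduce two figures shown in the Fitbit app, because Fitbit supplies neither the figures nor the algorithm. Two filters come before both metrics: "First, we will exclude days with less than 10 wearing hours [37] and remove the sleep period detected by Fitbit from calculation". The metrics are then defined in consecutive sentences:

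- Total stationary hours are "the sum of all sedentary minutes that had accompanying heart rate data during a selected day".
- The longest stationary period "will be calculated by the longest uninterrupted period of the day at which zero steps were taken".

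On wear, section 2.6.3 says that "participants will be instructed to wear the device during waking hours". On nights it says: "They will also be encouraged to wear the Fitbit at night, although this is optional". The device is to be charged once a week; neither the duration nor the time of day is given.

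The Monday message in section 2.6.5 contains "a weekly summary of sedentary time, the longest sedentary period, and a suggestion for extra sitting breaks", among other items. Step 4 chooses between praise, reinforcement and encouragement by the number of days on which the sedentary-hours goal was met.

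**The concern.** The two definitions treat wear differently. Requiring heart-rate data is a minute-by-minute check that the device is on the wrist. It protects total stationary hours from unworn time, but the longest-period rule does not carry it. A device on a bedside table records no steps, and without wear there is no sleep for Fitbit to detect and remove. The unworn night can then become the longest run of the day.

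What is at stake is the quality of the feedback. Tailored messages are one of the four intervention components, and the longest sitting period is something participants are asked to monitor and interrupt (section 2.6.3). A message reporting seven hours of unbroken sitting to someone who was asleep is wrong and may look irrelevant. Section 2.9.1 has participants rate the relevance of message contents, with a threshold of 75% agreement on each statement, so implausible figures could lower a rating for a reason unrelated to the concept being piloted.

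**Working it through.** The plan gives no figure to reproduce, so the check applies the written rule to illustrative days.

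**Inputs from the article.** A day is kept if wear is at least 10 h; detected sleep is removed; the longest zero-step run is taken (section 2.6.5, step 3). Night wear is optional (section 2.6.3). The 19:00–20:40 window in a Table 2 example message, 100 min, stands in for the true longest sitting bout.

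**Assumptions.** Unworn minutes carry zero steps; no sleep is detected while the device is off; the day runs midnight to midnight; apart from the 100-min bout, steps occur every 30 min while the device is worn.

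**Step 1: can unworn time pass the day filter?** A day with the minimum wear can hold 24 − 10 = 14 h of non-wear. Wear from 07:00 to 22:00 is 15 h, so that day is kept.

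**Step 2: longest run under each rule.** For 07:00–22:00 wear, the block from midnight to 07:00 is 7 × 60 = 420 min and the block from 22:00 to midnight is 2 × 60 = 120 min. The longer one is returned. The other rows follow in the same way.

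| Wear pattern | Wear (h) | Day kept | Rule as written (min) | With heart-rate condition (min) |
|---|---|---|---|---|
| 07:00–22:00, off at night | 15 | yes | 420 | 100 |
| 08:00–22:00, off at night | 14 | yes | 480 | 100 |
| 11:00–21:00, off at night | 10 | yes | 660 | 100 |
| Day and night, sleep detected | 24 | yes | 100 | 100 |
| Day and night, 2-h charge at 13:00 | 22 | yes | 149 | 100 |
| Day and night, 1-h charge at 13:00 | 23 | yes | 100 | 100 |

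**Step 3: charging.** With a step at 12:30, 29 zero-step minutes precede a charge at 13:00. A 2-h charge gives 29 + 120 = 149 min, which exceeds the true bout. A 1-h charge gives 29 + 60 = 89 min, which does not. Charging matters only when the unworn run outlasts the longest true bout.

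**Step 4: day boundary.** If the day were not cut at midnight, the 22:00–07:00 block would count whole: 9 × 60 = 540 min. Moving the boundary changes the size of the error but does not remove it.

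**The case against.** The strongest reply has four parts.

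- **Wear is not ignored.** The 10-hour day filter and the sleep removal apply to this metric too, and night wear is encouraged. A reader might infer that there is no wear filter at all; that is not so. Only the minute-level check is absent, and participants who sleep with the device on, with sleep detected, are unaffected.
- **The mechanism rests on something unstated.** The article does not say whether unworn minutes appear as zero steps or as missing. This stands as a limit on certainty. However, a heart-rate condition on sedentary minutes would be needed only if unworn minutes can be labelled sedentary, so the assumption is plausible.
- **The article condenses a script.** The script may already break runs at gaps. That is possible, but the rule is stated explicitly and, as stated, gives the wrong answer.
- **The aim is to match the app.** An added condition might move the figure away from what participants see there. Since the team already uses heart rate to reproduce the other app figure, this is a weak reason to omit it here.

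Stronger readings are tempting but unsupported. One is that the error changes which type of message is sent; step 4 uses only the sedentary-hours goal, and that metric has the heart-rate condition. Another is that the suggested break windows are wrong; the article does not say how they are derived, and all the Table 2 examples are evening windows. A third is that participants can earn praise by wearing the device less, because stationary hours are not scaled to wear time. Less wear does record less sitting, but absolute hours fit goals set in hours and the aim of matching the app. Participants are also told to wear the device throughout waking hours, with reminders and telephone follow-up. Rescaling is a debatable trade-off, not a correction of an error.

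**Conclusion.** The point holds as a minor one. As written, the longest-period rule lacks the wear check applied to the companion metric in the preceding sentence, and neither upstream filter catches an unworn night that the protocol permits. Under the stated assumptions the reported figure is 420 to 660 min in the illustrative off-at-night days, whatever the true longest bout, provided that it is shorter than the unworn block. How many participants are affected depends on how many remove the device at night, which the article cannot tell us.

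The consequence is limited to the longest-period figure in the Monday message. It therefore touches intervention fidelity and possibly the rated relevance of the messages. A reader might infer that the trial's results are compromised. They are not: sedentary behavior is measured by activPAL (section 2.9.2), and feasibility uses dropout, valid Fitbit days and text responses (section 2.9.1). No outcome is computed from this metric.

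**What to change.** Define the longest stationary period as the longest zero-step run over minutes with accompanying heart-rate data, ending a run at any heart-rate gap. This extends to the second metric the condition already used for the first.

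The stored minute-level data in REDCap can settle the open assumption: inspect a few unworn nights to see whether steps appear as zero or missing, and check whether the script already breaks runs at heart-rate gaps. If it does, only the text needs correcting.

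If the script changes, record the date so that messages sent before and after can be told apart when the acceptability ratings are read. Messages already sent cannot be altered, and no outcome needs re-analysis. The cost is a few lines of code or one sentence of text.
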